**MOMMY ‐ MIND: Identification of Fecal Microbiome Biomarkers to Predict Risk of Neurodevelopmental Disorders**
* The prevalence of NDDs, such as ASD or attention deficit hyperactivity disorder (ADHD), has increased over recent years [80, 81]. Emerging studies suggest the actual involvement of the gut microbiome in regulating brain development [82, 83]. Nevertheless, any disturbance that could negatively influence brain functionality could also possibly lead to a range of neurodevelopment disorders [84]. Critical developmental windows that influence early behavioral outcomes have been identified, including both the prenatal environment and early postnatal colonization periods. The clearest data regarding the role of gut microbiota on neurodevelopment and psychiatric disorders are from animal studies; however, human data have begun to emerge, including an association between early colonization patterns and cognition [85].

**Figure 4 imo270068-fig-0004:**
[figure not shown]
MOMMY inception cohort projects. Studies derived from the MOMMY: MOMMY‐HEALTH, MOMMY‐Epi, MOMMY‐MAGIC, MOMMY‐FA, MOMMY‐COVID, MOMMY‐IBD, MOMMY‐GDM, MOMMY‐MIND, and MOMMY‐ATOPY.

In this MOMMY‐MIND study, we aim to leverage a well‐characterized prospective inception cohort MOMMY to determine the role of fecal microbiome markers as well as dietary factors in infants for predicting and detecting risk of NDDs in children, especially children with ASD, ADHD, and anxiety disorders. Estimation of sample size: The predicted probabilities for NDDs in our previous studies [4, 86] were used for sample size calculation. The mean difference of predicted probabilities between subjects with and without NDDs was 0.12 (0.35 vs. 0.47). The population standard deviation was 0.138 based on our over 1600 Hong Kong population data set. Based on these preliminary data, 250 participants per group are required for a two‐tailed chi‐square test with a type I error of 0.05 and a power of 95%. According to the accumulative 25% prevalence of NDDs, 1000 consecutive infants will be recruited and assessed. A sample of healthy children, matched on gender, and sex, would serve as controls. All children will also be profiled by intelligence quotient (IQ), socio‐demographics, and family history of psychiatric conditions. We hypothesize that early life microbiome signatures are associated with, and may be predictive of the risk of NDDs in infants. We aim (1) to identify gut microbial markers in the first year of life, associated with, and predictive of ASD in preschool children; (2) To determine early life gut microbial signatures associated with, and predictive of ADHD and anxiety disorders in preschool children; (3) To delineate the association of early life gut microbiome and IQ in pre‐school children; (4) To investigate the impact of maternal diet and infants' diet on microbiome and NDDs in pre‐school children. The clinical identification of neurodevelopmental/psychiatric disorders will be a 2‐stage process, first by parent‐filled questionnaire, followed by a standardized confirmatory diagnostic interview.

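### MOMMY-MIND: the stated test, inputs and 250 per group at 95% power do not fit together, and 250 is recovered only if 0.138 is a variance and the test compares means

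*Protocol article*

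**What the plan says.** The paragraph is in the Protocol article, section 3 (Studies derived from MOMMY), in the MOMMY-MIND text that follows Figure 4.

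- **Effect:** "The mean difference of predicted probabilities between subjects with and without NDDs was 0.12 (0.35 vs. 0.47"). This is a difference between two means of a continuous score.
- **Spread:** "The population standard deviation was 0.138", attributed to a Hong Kong data set of over 1600.
- **Result:** "250 participants per group are required for a two‐tailed chi‐square test with a type I error of 0.05 and a power of 95"%.
- **Scaling up:** "According to the accumulative 25% prevalence of NDDs, 1000 consecutive infants will be recruited and assessed".
- **Controls:** healthy children "matched on gender, and sex, would serve as controls".

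The numbered aims that follow treat ASD separately from ADHD and anxiety disorders. The calculation covers pooled NDD only.

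**The concern.** The inputs describe a comparison of means, but the test named is for proportions. A reader who tries to check 250 has to discard either the standard deviation or the chi-square test, and the two choices give requirements that differ twelvefold (36 and 434 per group). The stated 95% power therefore cannot be attached to an analysis as written.

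The figure of 250 sets the recruitment number, since 250 / 0.25 = 1000. The true spread of the score also decides whether anything is left for the separate ASD, ADHD and anxiety aims, which will have fewer cases than the pooled group.

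**Working it through.** **Inputs, all from the MOMMY-MIND paragraph:** means 0.35 and 0.47, difference 0.12; SD 0.138; two-sided alpha 0.05 (z = 1.960); power 95% (z = 1.645); 250 per group; prevalence 25%.

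**1. Comparison of means, SD 0.138 as stated.**
n per group = 2 × [(1.960 + 1.645) × SD / difference]² = 2 × (3.605 × 0.138 / 0.12)² = 34.4, so 35. The t-test (standardised difference 0.12 / 0.138 = 0.87) gives 35.4, so 36. At 250 per group the power exceeds 99.99%, and the difference detectable with 95% power is 3.605 × 0.138 × √(2/250) = 0.044 by the normal formula (0.0446 by the t-test, about 0.045).

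**2. Chi-square test, 35% versus 47%.**
n per group = [1.960 × √(2 × 0.41 × 0.59) + 1.645 × √(0.35 × 0.65 + 0.47 × 0.53)]² / 0.12² = (1.960 × 0.6956 + 1.645 × 0.6904)² / 0.0144 = 433.6, so 434.

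| Variant at 95% power | n per group |
|---|---|
| Pooled variance | 434 |
| Unpooled variance | 431 |
| Arcsine | 435 |
| Continuity-corrected | 451 |
| One-sided | 361 |

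At 250 per group the two-sided power is 78.0% (about 75% with continuity correction). With 250 cases and all 750 non-cases it is about 92%. Even at 80% power the test needs 263 per group.

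**3. Comparison of means, 0.138 taken as a variance.**
SD = √0.138 = 0.371. n per group = 2 × (3.605 × 0.371 / 0.12)² = 249.1, so 250. The t-test gives 250.03, and power at 250 is 95.0%. Of the readings tried, this is the only one that recovers 250 at the stated alpha and power. It requires both the label on 0.138 and the name of the test to be wrong.

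**4. Can the article settle which label is right?**
No. A score confined to 0–1 with mean 0.35 can have an SD of up to √(0.35 × 0.65) = 0.477, so 0.371 is wide but possible, and 0.138 is also possible. If the SD is 0.371, 36 per group would have only 27% power.

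**5. Separate disorders.**
The article gives no case numbers per disorder. For illustration, assume 30 or 50 cases against 750 controls. The difference detectable with 95% power is 3.605 × SD × √(1/cases + 1/750).

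| Assumed cases | SD 0.138 | SD 0.371 |
|---|---|---|
| 30 | 0.093 | about 0.25 |
| 50 | 0.073 | about 0.20 |

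With SD 0.138 both lie below the planning difference of 0.12. With SD 0.371 both lie well above it.

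**6. Scaling.** 250 / 0.25 = 1000 is correct. Keeping a chi-square test at 95% power with equal groups would imply 434 / 0.25 = 1736 infants.

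**The case against.** The strongest defence is that 250 is not arbitrary. Step 3 reproduces difference, alpha, power and size together, which points to two mislabels in the text and not to a faulty calculation. On that reading the size, power and recruitment all stand. This is a fair inference and it limits the consequence. It does not rescue the paragraph, because it requires two of its statements to be wrong, and the article calls 0.138 a standard deviation without qualification.

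A reader might be tempted by stronger conclusions that the document does not support:

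- **That the sub-study is about seven times too large and has spare power for each disorder.** This holds only if 0.138 is confirmed as an SD.
- **That it is underpowered at 78%.** This needs a dichotomised outcome. The paragraph describes none; only the name of the test suggests it.
- **That attrition lowers the power further.** The paragraph speaks of 1000 infants recruited and assessed, and 25% of 1000 assessed infants is already 250. Nothing shows that the 1000 is counted before losses.
- **That cases and controls will be confounded by age.** The matching phrase does name one variable twice. That age was the intended second factor is plausible but unconfirmed, and Table 1 sets infant stool collection at scheduled visits, which limits differences in sampling age.

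**Conclusion.** The inconsistency holds as the text stands: test, inputs, size and power cannot all be true. The requirement at 95% power is 36 per group (means, SD 0.138), 250 (means, SD 0.371) or 434 (chi-square test, 35% versus 47%). The second matches the stated figure and is the likeliest origin, but this is an inference that only the source data can confirm.

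The consequence depends on that check. If 0.138 is a variance, two labels change and the numbers stand, but the illustrative per-disorder comparisons are weak at the planning difference. If it is an SD, 250 per group is far more than the pooled comparison needs. If a dichotomised chi-square test is truly meant, the stated 95% is really 78%, or about 92% against all non-cases. The per-disorder figures rest on assumed case counts. The duplicated matching variable is a secondary wording error.

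**What to change.** 1. Replace the chi-square test with a comparison of mean predicted probability (two-sample t-test or regression).
2. Check in the source data whether 0.138 is an SD or a variance, then restate:
   - If it is a variance, keep 250 per group at 95% power and correct the label to SD 0.371.
   - If it is an SD, state 36 per group as the requirement, and that 250 per group detects 0.045 at 95% power.
3. If a dichotomised comparison is really intended, define the cut-off and restate the power as 78% (250 versus 250) or about 92% (250 versus 750).
4. Keep the 1000 infants. Add the expected number of cases and the detectable difference for ASD, ADHD and anxiety disorders under the confirmed SD.
5. Correct the second matching factor. Age at sampling is a candidate for the sponsor to confirm.

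The cost is one look at the source data and one rewritten paragraph. No extra recruitment is needed unless the sponsor keeps a chi-square test and insists on 95% power. The restated power may be less favourable than the present claim.

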## POTENTIAL BIAS AND LIMITATIONS

4

There are valuable contributions of established birth cohorts, such as CHILD (Canada), GUSTO, and S‐PRESTO (Singapore), in advancing early‐life microbiome research. Key findings from these cohorts, including environmental and maternal determinants that influence the development of the infant's multi‐kingdom microbiome (bacterial and fungal), as well as links to child health outcomes (growth, atopic eczema) [87, 88, 89, 90], have been foundational to the field. Most large‐scale microbiome cohorts are Western (e.g., CHILD, TEDDY) or city‐specific (e.g., GUSTO). MOMMY's inclusion of diverse Chinese populations with distinct dietary, environmental, and genetic influences on microbiome development addresses the underrepresentation of these groups in microbiome research. In the meantime, it may introduce potential biases in our cohort and may limit the generalizability of our findings. Therefore, our results will also be validated in other birth cohorts using a publicly available data set. Unlike many cohorts with limited follow‐up, MOMMY tracks mother‐infant dyads from pregnancy through early childhood, capturing dynamic microbiome transitions (e.g., weaning, antibiotic exposures) with high‐resolution sampling. MOMMY combines microbiome data with detailed metadata (e.g., maternal diet, urban/rural disparities) and host genomics, enabling mechanistic insights into culturally specific drivers of microbiome assembly.

## CONCLUDING REMARKS

5

In this perspective, we provide a profile of the bio‐samples and comprehensive assessments collected in MOMMY and define the MOMMY inception cohort used to evaluate microbiome determinants of major clinical outcomes. The long‐term goal of MOMMY is to identify environmental, dietary, and microbial determinants (including psychosocial factors) in early life that trigger (perhaps through genetic susceptibility) or protect against common childhood diseases, allergic diseases, (eczema, wheezing, asthma, and allergic sensitization) and NDD. Operating multi‐omics data from various biosamples, the MOMMY cohort will significantly enhance the resolution of mechanisms of microbiome transmission from mother to baby. Taken together, the MOMMY cohort provides the translational value of innovations for disease early diagnosis, prevention, or treatment based on strain‐level manipulation of the gut microbiome.

Overall, that's just the start of the effort and will be the first largest prospective Asia population‐based birth cohort study that is ambitious to uncover the link between the parental and newborn microbiome, segregating favorable and unfavorable taxa with multiple measures of both dietary intake on health and disease in early life development. As a resource, these results will aid both in the utilization of the gut microbiome as a biomarker for disease risk and in strategies for reshaping the microbiome to improve personalized health, which will have significant implications for preventive interventions and guide future public health and government policy development.

## ETHICS STATEMENT

This study has been registered at ClinicalTrials.gov (NCT04117321) and has been approved by the Joint Chinese University of Hong Kong – New Territories East Cluster Clinical Research Committee (reference number 2019.243).

## Data Availability

The MOMMY Study welcomes collaboration, and we are keen to establish MOMMY as a research platform. To protect participant's privacy and comply with the informed consent, participant metadata used in the current study cannot be deposited in public repositories. According to our institutional data sharing policy, data sharing requests may be submitted with a written proposal as a part of a collaboration effort. The proposal should detail the intended use of the data. These requests are reviewed based on scientific merit and ethical considerations, including participant consent. Data sharing will be undertaken if the proposed projects have a sound scientific rationale or potential societal benefit. We ensure that restrictions related to subject confidentiality and consent are addressed by aggregating and anonymizing identifiable data. Additionally, all indirect identifiers that could lead to deductive disclosures will be removed. Data recipients are required to enter formal data sharing and collaboration agreements, which describe the conditions for release and requirements for data transfer, storage, archiving, publication, and intellectual property. Supplementary materials (graphical abstract, slides, videos, Chinese translated version, and update materials) may be found in the online DOI or iMeta Science http://www.imeta.science/imetaomics/.
